#### Missing values

In the event that missing data occur, we will attempt to contact participants and obtain the data or to find out why the questionnaires or items are missing, and document the reasons for missing data. The planned analyses employ a mixed models approach that do not require complete data on all participants but make the assumption that data are missing completely at random; this assumption will be examined.

### Statistical analyses

The primary outcome measure will be the 5A score as described in (section Primary outcome measure: 5As score). The primary analysis will use a mixed effect model to compare mean 5As scores between and within each group for each of the three time points: baseline, immediately post-intervention, and follow-up. The primary hypothesis (H1) is: Clinicians who complete the communication intervention will increase their use of all 5As for all visits in which the topic of physical activity is raised as judged by audio-recordings of office visits in the post-intervention period (immediately post and at one year) compared to baseline. Figure 2 shows the analysis plan for hypothesis testing and exploratory outcomes.

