**Figure 1 F1:**
[figure not shown]
Study Schema.

The project is a two-arm randomized pragmatic trial to pilot a communication training intervention for primary care clinicians (n=13) on use of the 5As to promote physical activity in underserved patients. The intention of training focuses on clinicians to communicate effectively using the 5As and patient-centered communication skills firmly linked to a theory of human motivation (Aim 1). Clinicians are randomly assigned to two groups. Group 1 participates in the training intervention first; Group 2 receives the intervention six months later. The primary outcome is the frequency and quality of clinician use of the 5As during routine office visits, post-intervention compared to baseline. Secondary outcomes and potential mediators are changes in patients’ perceived competence to adopt physical activity (Aim 2) and clinician autonomy support of physical activity with their patients (Aim 3). Given the myriad of barriers reported in the literature, another secondary outcome is whether clinicians believe that the intervention addresses pertinent barriers to promoting exercise (Aim 4). Exploratory outcomes are other potential mediators of the intervention’s effect and the effect of the intervention on actual physical activity levels in a subset of participants. The schema shows the overall study design and timeline.

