### Data management

All questionnaires and measurements will be collected and entered into a secure protected database by the Research Assistants. Data will be entered on scannable forms and electronically sent to an Access database. After scanning, data will be audited visually for errors. SAS statistical packages are used for the analyses. Unless otherwise stated, all statistical tests will be performed at the two-tailed 5% level of significance. Likewise, 95% confidence intervals will be constructed for estimation of effects (e.g., difference in mean 5A scores across time points).

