**Figure 2 F2:**
[figure not shown]
Mediators and moderators to be assessed in exploratory analyses.

The clinicians will be included as a random effect, and intervention group, time, and baseline 5A scores will be included as fixed effects. The interaction between treatment and time will be used to assess whether the treatment effect (of the intervention) changes with time.

Secondary analyses include similar modeling approaches for the secondary outcome variables: autonomy support (mHCCQ), patient perceived competence (PCS) and clinician feasibility (PAL). Clinician feasibility will also be qualitatively analyzed using the process evaluation data and individual clinician exit interviews. The secondary hypotheses (H2-H4) are as follows:

H 2: The intervention will increase clinician use of the PCC construct autonomy supportiveness as assessed by the mHCCQ in the post-intervention period (immediately post and at one year) compared to baseline.

H 3: The intervention will increase patient perceived competence (accessed via the PCS) for adopting physical activity.

H 4: Specific patient recall of the Assist and Arrange will be associated with the greatest patient perceived competence to adopt physical activity compared to recall of Ask, Advise, or Assess.

Hypotheses 2–4 will be tested by measuring the changes in the mHCCQ, PCS, and PAEI scores, respectively, for patients seen by clinicians in Group 1 in the post-intervention period (immediately post and at one year) compared to baseline. compared to the Group 2 baseline and Group 1 baseline. We will also compare change in the 5A scores for Group 2 post-intervention compared to Groups 1 and 2 baseline scores.

Exploratory analyses will use a similar approach to that used for the primary analysis, to examine whether the primary outcome (5A score) was mediated by patient perceived competence (PCS score), clinician autonomy supportiveness (mHCCQ score), or patient recall of the 5As (PAEI score). Additional exploratory analyses will examine the role of selected factors that may moderate the relationship between the intervention and the 5A score: continuity of care, patient socio-demographic variables, patient BMI, baseline health, health behaviors, health literacy, and competing demands. Regression-based statistical models will be constructed and examined. The Diagram below shows the inter-relationship of the mediating and moderating factors to be explored in this analysis.

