### Sample size and power

The primary goal of this study is to evaluate the influence of a clinician communication intervention on use of the 5As in communication about physical activity in the post-intervention period (immediately post and at one year) compared to baseline as assessed by audio-recorded data. The sample includes a planned maximum of 15 clinicians (eight in Group 1 and seven in Group 2) measured at three (Group 1) or four (Group 2) time points. The measurements consist of a total of 25 audio-recorded patient visits from each clinician distributed across each of the evaluation points: approximately 10 recordings at baseline and seven or eight each at post- and follow-up points. Of the planned 375 recorded visits, we estimate up to 20% may be excluded from the analysis due to the patient or clinician shutting off the recorder, or equipment malfunction, thus leaving approximately 300 recorded visits (about seven per clinician per time point, or 20 total per clinician) for analysis. Pilot data with 46 recorded visits from eleven physicians showed that the average 5A score was 0.74, with a standard deviation of 1.06. Thus, with 15 clinicians and 20 patients per clinician, we will have 80% power to detect a difference of 0.54 between Groups 1 and 2, using a two-sided t-test at 0.05 significance level.

The final analyses will use a mixed effects model to incorporate correlations between the observations made by the same physician. The variance in 5A scores taken from patients within a single physician's patient panel will likely be smaller than the variance of scores taken from patients between different physicians, i.e. the intraclass correlation coefficient (the ratio of between-physician variance to the sum of between- and within-physician variances) will be larger than zero. We have conducted a series of power analyses taking this clustering into effect using a Mann–Whitney two-sample t-test of means.

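### The primary hypothesis, the power statement and the primary analysis name different deciding comparisons, and a before-after rise alone could satisfy the hypothesis

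*Protocol article*

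**What the plan says.** All places are in the protocol article.

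- **Hypothesis.** Statistical analyses: "The primary hypothesis (H1) is: Clinicians who complete the communication intervention will increase their use of all 5As", judged immediately after training and at one year against baseline. No comparison group is named. The text does not say whether one or both later points must succeed. The aims at the end of the Background give the same hypothesis.
- **Outcome.** Study design: "The primary outcome is the frequency and quality of clinician use of the 5As during routine office visits, post-intervention compared to baseline". The opening of Sample size and power describes the study's main goal in the same before-after terms.
- **Power.** Sample size and power: "80% power to detect a difference of 0.54 between Groups 1 and 2, using a two-sided t-test at 0.05 significance level".
- **Analysis.** Statistical analyses: the primary mixed model is to "compare mean 5As scores between and within each group for each of the three time points".
- **Further 5As comparisons.** Statistical analyses: "The interaction between treatment and time will be used to assess whether the treatment effect (of the intervention) changes with time". The paragraph on the secondary hypotheses adds: "We will also compare change in the 5A scores for Group 2 post-intervention compared to Groups 1 and 2 baseline scores".
- **Error level.** Data management: "Unless otherwise stated, all statistical tests will be performed at the two-tailed 5% level of significance". Nothing else is stated for the primary outcome.

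**The concern.** The trial randomises clinicians to early or wait-list training, so its protected evidence is the comparison of trained with not-yet-trained clinicians. H1 does not use that comparison, the power statement does, and the primary analysis covers both kinds without saying which decides.

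Two things are at stake. First, with several candidate tests each at 5%, the error rate attached to a positive primary result is no longer 5%. Second, the candidates can give opposite answers. Design limitations and other considerations lists Hawthorne effects, spill-over and cross-contamination as concerns. If both groups rose for such reasons, H1 would be met while the randomised comparison showed nothing. Larger trials are to be built on these results, so a before-after rise taken for a training effect would mislead their planning.

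**Working it through.** **1. Which contrast does the stated power describe?** Inputs from Sample size and power: SD 1.06, 8 and 7 clinicians, 20 visits each, difference 0.54.

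- With 160 and 140 visits, SE = 1.06 × √(1/160 + 1/140) = 0.1227. The detectable difference at 80% power is 2.802 × 0.1227 = 0.344, and power for 0.54 is 0.99. A plain t-test on all visits does not give the stated 80%.
- With about 8 visits per clinician (64 and 56), SE = 0.194, the detectable difference is 0.543 and power is 0.795.
- Alternatively, a design effect of (0.54/0.3437)² = 2.47 gives 80%. That corresponds to an ICC of (2.47 − 1)/19 = 0.077.

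On any of these routes the powered quantity is a difference in level between groups. It is neither H1's before-after change nor a difference in change.

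**2. Counting the comparisons.** Between groups there are three time points, so three differences. Within groups there are two changes from baseline in each of two groups, so four. The baseline group difference cannot be a training effect, which leaves six.

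**3. Chance of at least one false significant result.** The assumptions are:

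- any one significant test counts, and each test is valid on its own at two-sided 5%;
- a random clinician intercept with ICC 0 to 0.5 (the document says only that it exceeds zero);
- 7/7/7 or 8/6/6 analysable visits per clinician, the latter being 80% of 10/7.5/7.5.

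The independence column is 1 − 0.95^k. The last column comes from 400,000 simulated null draws per setting, with the correlation that shared means and clinicians create.

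| Reading | Tests (k) | If independent | With correlation |
|---|---|---|---|
| H1, Group 1, two later points | 2 | 0.098 | 0.09 |
| H1, both groups | 4 | 0.185 | 0.17–0.18 |
| Between and within, without baseline difference | 6 | 0.265 | 0.23–0.24 |
| One deciding contrast | 1 | 0.05 | 0.05 |

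**4. Can the candidates disagree?** Suppose both groups rise by 0.54 with no training effect (assumed ICC 0.07; 8 baseline and 6 post visits per clinician).

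- Group 1 change: SE = 1.06 × √[0.93 × (1/8 + 1/6)/8] = 0.195. Then 0.54/0.195 = 2.77, and the test is significant about 79% of the time.
- Between groups the true difference is zero, so that test is significant about 5% of the time.

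**5. Power of a randomised contrast at one wave** (same visit counts, normal approximation).

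- As a difference in change: SE = 1.06 × √[(1 − ICC) × (1/8 + 1/6) × (1/8 + 1/7)]. At ICC 0, SE = 0.296 and power for 0.54 is 0.45. At ICC 0.2, SE = 0.265 and power is 0.53.
- With baseline adjustment, replace (1 − ICC)(1/8 + 1/6) by p − ICC²/b, where p = ICC + (1 − ICC)/6 and b = ICC + (1 − ICC)/8. At ICC 0 this is 0.167, SE = 0.224 and power 0.67. At ICC 0.1 it is 0.203, SE = 0.247 and power 0.59. At ICC 0.2 it is 0.200, SE = 0.245 and power 0.60.

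Neither form reaches 80%. A t reference on so few clinicians would lower these figures somewhat.

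**The case against.** The strongest reply is that the text does label H1 as the primary hypothesis and repeats its before-after contrast in several places, so the primary question is not wholly open. Multiplicity rules are commonly left to an analysis plan that is not shown. This is also a pilot, with 95% confidence intervals planned. The authors say they will use the two-group design and a check on Group 2's scores to look for Hawthorne and contamination effects.

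Much of this stands. The absence of an alpha split or testing order is not itself the fault. The 79% versus 5% example is a deliberate extreme, and the protocol lists such effects as concerns without predicting them. H1 is also directional: among the six comparisons, a false result in the favourable direction occurs about 0.12 to 0.13 of the time, against 0.025 for one test.

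The conflict between the statements remains. No analysis plan can honour a before-after primary hypothesis, a between-group power claim and an all-comparisons primary analysis as the single basis for a conclusion.

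A reader might go further and infer a seven-test primary family with a false-positive rate of about 0.25 to 0.26. The arithmetic is right for seven correlated tests, but the documents do not support that as the headline. It counts the baseline difference and passes over H1. The interaction and the comparison of Group 2 with both baselines cannot be added either, because neither is labelled primary.

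**Conclusion.** The point holds as an inconsistency in the protocol's own text: the deciding primary comparison is stated in incompatible ways. Followed as written, H1 could be declared met on an uncontrolled rise.

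The error-rate consequence is a range, about 0.09 to 0.24 depending on the reading, against the stated 0.05. It rests on a rule the document does not state (any one significant result suffices) and on an assumed ICC, though the ICC matters little. The inconsistency itself rests on no assumption. It should be corrected before analysis.

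**What to change.** In Statistical analyses, name one deciding test: the baseline-adjusted Group 1 versus Group 2 difference in 5As score at Group 1's post-training wave, at two-sided 5%. Represent Group 2 by its second assessment before its own training.

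- **Reconcile that assessment.** Group 2 (wait-list) places it at 9–12 months and Assessing cross-contamination at months 12–15. Sample size and power gives Group 2 four time points but allots recordings to only three (10, then seven or eight twice).
- **Label as supportive**, with 95% confidence intervals: the within-group changes, the follow-up comparisons, and Group 2 against the pooled baselines. The follow-up comparison should not be confirmatory, because Group 2 is trained six months after Group 1 and there may be no untrained comparator by then.
- **Align** H1 and the outcome statement in Study design with the named test.
- **Restate the power** for this contrast, with an explicit ICC.

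Most of this is wording. Recordings may have to be reallocated or added if Group 2's second pre-training wave is not already within the planned 25 visits per clinician. A favourable within-group change alone could no longer be reported as a positive primary result, and the stated power becomes less favourable.

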### Group 2 (wait-list)

The clinician baseline assessment for Group 2 is identical to that for Group 1. The Group 2 assessment occurs at 0–3 months (concomitant with the Group 1 clinician baseline) and again at 9–12 months (concomitant with the Group 1 post-intervention assessment.)

Group 2’s clinician training intervention occurs in the same manner as described in the section, Description of Intervention (section 2.11) for Group 1. Standardization of both Group 1 and Group 2’s training intervention sessions is assessed by audio-recording all sessions and ensuring that the key objectives of each session are met using a pre-developed checklist and via rating by a trained research staff member not involved in delivering the intervention.

Group 2’s Post-Intervention Assessment occurs immediately post-intervention and at six months post-intervention in the same manner as described previously for Group 1 (section Post-Intervention Clinician Assessment). As with Group 1, Group 2 clinicians also complete a survey asking about the feasibility of the intervention and individual exit interviews.

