### Evaluation and measures

#### Primary outcome measure: 5As score

The primary outcome measure is the 5As score, a score of the frequency and quality of 5As discussions about physical activity. Based on our previous pilot study and others’ published work [11,15,53,54] we developed a coding form to capture the 5As from audio-recorded office visit discussions. The 5As score has two components: 1) the sum of each A of the 5As occurring in each office visit when the topic of physical activity is raised (range 0/no As used to 5/all As used) and 2) a rating of the quality of each A when it occurs (ranging from 1–3 based level of detail from minimal to intensive). The 5As score is measured at baseline, immediately post-intervention, and at six months follow-up for Groups 1 and 2. The 5As score is assessed by trained research staff blinded to clinician and time point.

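### As written, the primary model compares trained with trained clinicians after baseline; the concurrent untrained Group 2 assessment is not named as the comparator

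*Protocol article*

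**What the plan says.** All references are to the protocol article.

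- **Design** (Study design): "Group 1 participates in the training intervention first; Group 2 receives the intervention six months later". Every clinician is eventually trained.
- **Outcome schedule** (Primary outcome measure): "The 5As score is measured at baseline, immediately post-intervention, and at six months follow-up for Groups 1 and 2".
- **Primary model** (Statistical analyses): it will "compare mean 5As scores between and within each group for each of the three time points: baseline, immediately post-intervention, and follow-up". Clinician is a random effect; group, time and baseline score are fixed effects. The treatment-by-time term is there to show whether the effect changes over time. H1 is a post-versus-baseline statement with no comparator group.
- **H2 to H4** (Statistical analyses, text after Figure 2): scores are compared "for patients seen by clinicians in Group 1 in the post-intervention period (immediately post and at one year) compared to baseline", followed by a fragment that adds the Group 2 and Group 1 baselines as references. A further comparison is "change in the 5A scores for Group 2 post-intervention compared to Groups 1 and 2 baseline scores".
- **Wait-list group** (Group 2): it is assessed at 0–3 months and "again at 9–12 months (concomitant with the Group 1 post-intervention assessment". Its own immediate post-intervention assessment comes after its own training.
- **Second untrained assessment** (Assessing cross-contamination): Group 2's two baselines are compared with each other to look for contamination.
- **Sample size and power**: clinicians are "measured at three (Group 1) or four (Group 2) time points", with "approximately 10 recordings at baseline and seven or eight each at post- and follow-up points". The stated 80% power is for a difference of 0.54 between Groups 1 and 2.

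**The concern.** A wait-list design identifies the training effect during the window when the early group is trained and the wait-list group is not. The data for that window are to be collected, but the stated primary model has no cell for them. Its between-group comparison after baseline sets trained clinicians against trained clinicians, and its within-group comparison is before versus after.

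Two things are at stake. First, the between-group result could be close to zero even if training works well, and could be misread as no effect. Second, the before-after result credits to training any secular change, any practice-wide change and any reaction to being recorded. The power statement promises a between-group test that the model, as described, does not contain.

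**Working it through.** **1. Cells of the model as written**

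| Time point in model | Group 1 | Group 2 | Expected Group 1 minus Group 2, if training adds 0.54 in both |
|---|---|---|---|
| Baseline | untrained | untrained | 0 |
| Immediately post | trained | trained | 0.54 − 0.54 = 0 |
| Follow-up | trained | trained | 0.54 − 0.54 = 0 |

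Group 2 reaches each post-training point about six months later than Group 1, so calendar drift over that lag would appear in the difference. The training effect would not. A difference of 0.54 arises only against Group 2's second pre-training assessment: 0.54 − 0 = 0.54.

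**2. Before-after contrasts**

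The expected value is the training effect plus drift. The documents give no drift figure. For an assumed drift of 0.1, 0.2 or 0.3 As per visit, the share of the 0.54 target is 0.1/0.54 = 19%, 0.2/0.54 = 37% or 0.3/0.54 = 56%.

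**3. Recordings**

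10 + 7.5 + 7.5 = 25 per clinician, and 15 × 25 = 375. The split names three points. Group 2 has four, and no number is explicitly given for the second pre-training one.

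**4. Timing**

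- Group 1's first post-training assessment is at about 6 months from baseline (Post-intervention clinician assessment) but at 9–12 months in the Group 2 section.
- Group 2's second baseline is at 9–12 months in the Group 2 section but at months 12–15 in the cross-contamination section.

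**5. The stated power**

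Inputs from Sample size and power: SD 1.06, difference 0.54, two-sided 0.05, 8 and 7 clinicians. The normal approximation is power = Φ(0.54/SE − 1.96), with SE = 1.06 × √(1/n₁ + 1/n₂).

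- All 20 visits per clinician (160 v 140): 99.3%.
- 7 visits per clinician (56 v 49): 74.0%.
- 8 visits per clinician (64 v 56): 79.5%.

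The 80% is not reproduced from 20 visits per clinician without clustering. It is close to the result for 8 visits per clinician at one time point with no clustering. This mismatch is a separate matter, but it shows that the figure cannot simply be carried over to a new contrast.

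**6. Power for the concurrent contrast**

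Suppose Group 2's 25 recordings are divided 7/6/6/6 and 20% are lost, as the plan allows. Group 1 then has 7.5 × 0.8 = 6 usable visits per clinician at its first post-training point, and Group 2 has 6 × 0.8 = 4.8 at its second pre-training point. With m₁ = 6 and m₂ = 4.8:

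SE² = 1.06² × {[1 + (m₁ − 1)ICC]/(8m₁) + [1 + (m₂ − 1)ICC]/(7m₂)}

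| ICC (assumed) | SE | 0.54/SE | Power |
|---|---|---|---|
| 0 | 0.238 | 2.26 | 62% |
| 0.05 | 0.263 | 2.05 | 54% |
| 0.10 | 0.285 | 1.89 | 47% |
| 0.20 | 0.325 | 1.66 | 38% |

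These figures ignore baseline adjustment, which could raise power, and the small number of clinicians, which lowers it.

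**The case against.** The strongest reply is that a concurrent comparison was probably intended. Group 1's points at about 6 and 12 months from baseline, and H1's mention of one year, fit a calendar axis. The second Group 2 assessment is described as concomitant with Group 1's post-training one, and power is stated between groups. That stands as evidence of intent. It does not settle the text: the model and the outcome section name the points by training for both groups, and Group 2 has a fourth point that the three-point model omits.

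The reply also limits how far the criticism goes. A reader might infer three stronger things that the document does not support:

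- **That H2 and H3 have no control at all.** A Group 2 baseline is named as a reference. If the second one is meant, the comparison is concurrent. The sentence is garbled and does not say.
- **That drift and reactivity are ignored.** Comparing Group 2's two untrained assessments captures them, mixed with contamination. The limitations section says spillover and Hawthorne effects will be assessed using the two-group design. Neither statement makes the concurrent contrast the primary one.
- **That no recordings exist for Group 2's second pre-training point, or that extra visits are needed.** Recordings are said to be spread over all evaluation points, so the baseline 10 might be shared between the two. The division is unstated, not shown to be zero.

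The two figures are not visible and the analysis plan is not at hand. However, the article itself states the model, time points, hypotheses and powered contrast, and these do not fit together.

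**Conclusion.** The point holds for the text as written. After baseline, the primary model's between-group cells are trained versus trained, with an expected difference of 0 if training works equally in both groups and there is no drift. H1 is a before-after statement, so drift enters it one for one. The only untrained Group 2 data concurrent with Group 1's post-training data are explicitly assigned just to the contamination check, although power is stated between groups.

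It would go too far to conclude that the trial cannot make a randomised comparison. The design collects the data needed; the plan fails to name the contrast. For H2 and H3 the finding is an unspecified comparator, not a missing one. Because this concerns the primary estimate, it should be settled before analysis, and the division of recordings before Group 2's second pre-training assessment.

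**What to change.** 1. Name one primary contrast: Group 1's first post-training recordings versus Group 2's second pre-training recordings in the same calendar window, adjusted for first-baseline scores.
2. Use the same contrast for the mHCCQ and PCS, and say which Group 2 baseline is meant wherever one is cited.
3. State how Group 2's 25 recordings are divided over its four points. A 7/6/6/6 split keeps the total at 375.
4. Reconcile the assessment times in the post-intervention, Group 2 and cross-contamination sections.
5. Label follow-up and before-after results as lacking a concurrent control.
6. Restate power for the named contrast with an explicit ICC.

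No extra patients are needed. The cost is precision: there are fewer visits at each Group 2 point, and a 7/6/6/6 split takes the first baseline below the 10 visits that the recruitment section expects to be sufficient. Under that split, power for 0.54 falls in the 62% to 38% range shown above, which the plan should disclose.
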